### Study Objectives

The objectives of this research were to evaluate the efficacy of the loose parts intervention versus outdoor play practice in standard early child care settings to:(1)improve children’s physical literacy, and increase time in PA and active outdoor play;(2)improve educators’ attitudes, beliefs, perceived competency, and intentions towards incorporating the intervention into practice;(3)increase parents’ and educators’ understanding of play in child health and development.

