#### 3.2.4. Photo Documentation and Elicitation, and Focus Groups

Photo documentation and elicitation, and focus group sessions, were conducted at the 3-month and 6-month stage of the loose parts intervention. Photo elicitation involved participants photographing something specific prior to meeting with the research team for discussion of their photos; photo elicitation has previously been used to explore children’s health, physical activity, school environments, play and recreation [49,50,51,52]. This strategy/process for observing, documenting, and sharing stories of children playing with loose parts was designed to highlight and support the educators’ role in the intervention. The strategy, introduced at the training session, involved taking photographs accompanied by a documentation form focused on physical literacy, fundamental movement skills, and the educators’ role. Educators were asked to photograph, document, and submit examples of loose parts play that “caught their attention” as often as they could. Feedback, assistance and encouragement were made available throughout the intervention.

At the 3-month stage, all intervention participants were invited to attend a photo elicitation sharing and focus group activity to explore and share their experiences and to document changes they noted in their attitudes, beliefs, perceived competency, and intentions towards incorporating loose parts into the outdoor play environment. Each attendee (9 from original cohort; 15 from new cohort) was asked to bring a photo with documentation that demonstrated compelling evidence of how loose parts play supports physical literacy. The participants were organized into small groups (3 to 4 per group) to ensure that there would be opportunities for sharing between centres. Each focus group had a facilitator and a note-taker, and was audio-recorded. At the 6-month focus group sessions, both intervention and control centres were invited to participate. At the completion of these focus group sessions, the control groups received their loose parts kits.

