During the photo elicitation sharing activity the educators described the play patterns of the children in the photos and highlighted how active play with loose parts helped children learn fundamental movement skills which supports their physical literacy development. The stories provided more context and allowed for better understanding of play in healthy child development. It was a catalyst for in-depth discussions and served to trigger comments from other participants about their own experiences. This activity was followed by a series of focus group questions divided into several categories: outdoor active play, loose parts, risk-taking, policies, and challenges/benefits of the intervention. These focus groups, which lasted approximately 45 to 60 min, allowed for more in-depth exploration of what made it challenging, or what assisted them in using the loose parts in their daily activities. On-site focus groups were facilitated for the two child care centres that did not attend the original session (4 educators).

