### 3.3. Parents

#### 3.3.1. Parent Survey

Parents completed a 10 to 15-min survey at baseline with questions pertaining to themselves and their child, to better understand how children engage in active outdoor play and the factors potentially involved. The first section of the survey gathered information on parent demographics, physical activity participation (parent and child), sleep (child), sedentary behavior (parent), and parent perceptions of their child’s physical literacy. Parent perceptions concerning the level of risk associated with children’s physical activity/play behavior, and affordances for risk taking during physical activity/play, were also assessed. A total of 85 families completed the parent survey; 76 from the original cohort, and 9 from the new cohort.

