#### 3.3.2. Parent Interviews

At the end of the 6-month intervention, a subsample of parents in the intervention and control groups was invited to participate in parent interviews. Each director was asked to recommend two to four parents who might be willing to continue their involvement in the PLEY project and these parents were then invited to participate. The interviews were conducted by a facilitator and audio-recorded, with the assistance of a note-taker at 10 sites with 18 parents (individually or in small groups). The semi-structured interviews asked questions related to a typical day for their child both indoors and outdoors with a focus on active outdoor play, and explored the who, what, when, and where, of active outdoor play. Interviewers probed whether changing seasons and inclement weather influenced play decision-making. There was an overall interest in discovering what the parents learned about the project, about physical literacy and about the role of active outdoor play in their child’s healthy growth and development through participation in the PLEY project. Finally, there was an interest in learning about parent attitudes towards risk taking during play and seeing if those attitudes have an influence on parenting behaviors.

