### 3.4. Data Analysis

Descriptive statistics will be used to describe study participants (children, educators, parents) and participating child care centres. Linear mixed models with a random effect for centre will be used to determine if children exposed to the PLEY intervention had greater increases in physical literacy, PA, and time in active outdoor play, compared to children in the usual care group (control group). The model will include variables from the children’s TGMD-3 scores, PGMQ scores, and physical activity (as determined by accelerometry). The analysis will be approached from an intention-to-treat strategy. One of the primary outcome measures will be physical activity differences between the groups, while secondary outcomes include height, weight, BMI, and age. Additional analyses of the variables may include an analysis of covariance (ANCOVA) to determine differences in TGMD and PGMQ scores, with similar secondary outcomes of height, weight, BMI, and age, and again including a random effect to control for the clustered design. Missing data will be controlled for within the selected models and analyses. Significance level for these analyses will be set a *p* < 0.05.

Educator focus group data, and parent interview data, will be explored using qualitative analyses, to determine whether the intervention improved educators’ attitudes, beliefs, perceived competency, and intentions towards incorporating the intervention into practice; and increased parents’ and educators’ understanding of play in child health and development. These qualitative data will be transcribed and analyzed using NVIVO software to identify emerging themes. Children’s physical literacy and PA data will be examined in comparison with parent survey and interview responses, and educator survey and focus group responses, using a mixed methods approach. Data from the RE-AIM framework analysis and qualitative data emerging from the photo elicitation focus groups with intervention sites will determine the effectiveness of the intervention to achieve desired outcomes. The mixed methods approach will provide a more holistic understanding of the impact of the PLEY intervention on children’s physical literacy. Although the child measures only include some domains of physical literacy (e.g., physical competence and daily behavior) other aspects of the study including educator focus groups allow us to obtain data on the other components of physical literacy.

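### One-arm qualitative material, built partly on photos requested as proof of benefit, is given a role in determining effectiveness that it cannot carry

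*Protocol article*

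**What the plan says.** Section 3.4 (Data Analysis) names two joint sources, "Data from the RE-AIM framework analysis and qualitative data emerging from the photo elicitation focus groups", and gives them the verdict: the "qualitative data emerging from the photo elicitation focus groups with intervention sites will determine the effectiveness of the intervention to achieve desired outcomes". The same section says that educator focus groups and parent interviews will show whether the intervention improved educators' attitudes, beliefs, perceived competency and intentions, and whether it increased understanding of play.

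Section 3.2.4 describes the 3-month session: "all intervention participants were invited to attend a photo elicitation sharing and focus group activity". Each attendee "was asked to bring a photo with documentation that demonstrated compelling evidence of how loose parts play supports physical literacy". In the session the educators described the photos and "highlighted how active play with loose parts helped children learn fundamental movement skills which supports their physical literacy development". Control centres join the invitation only at 6 months, and receive their kits after those sessions.

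For parents, Section 3.3.1 says: "Parents completed a 10 to 15-min survey at baseline". No repeat is described. Section 3.3.2 describes one round of interviews at the end, in both arms: "Each director was asked to recommend two to four parents who might be willing to continue their involvement in the PLEY project".

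The Study Objectives put all three aims under one comparative heading, efficacy against standard practice. The third is to "increase parents’ and educators’ understanding of play in child health and development".

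**The concern.** A statement that an intervention is effective is a comparison with what would have happened without it. Section 3.4 assigns part of that statement to material from intervention sites, some of it requested because it shows benefit. Such material can say how educators used and experienced the kits. It cannot separate an effect of the kits from maturation, season, the training day or the wish to report success.

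Two conclusions are at stake. The first is any efficacy claim on objectives 2 and 3, which have no other outcome source described. The second is physical literacy, which is part of the primary aim: the end of Section 3.4 says that the child measures cover only some of its domains and that educator focus groups help to supply the rest. The one-sided material therefore also feeds the main construct.

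**Working it through.** The plan states no figure on this point, so the check sets the sections side by side.

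**Step 1. What each educator or parent source can contrast.**

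| Source | Before the intervention | Control arm | How informants or material were selected |
|---|---|---|---|
| 3-month photo sharing and focus group (3.2.4) | none described | not invited | those who attended; photo requested as supportive |
| 6-month focus groups (3.2.4) | none described | invited | those who attended |
| Parent interviews (3.3.2) | none described | included | recommended by directors; 18 parents at 10 sites |
| Parent survey (3.3.1) | yes | not relevant without a follow-up | families who completed it; no repeat described |

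No row gives a before-after measure in both arms. Rows 2 and 3 give a post-only comparison between arms; row 1 gives no comparison at all.

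**Step 2. Whether post-only is enough.** In a randomised trial, comparing the arms at follow-up can be valid without a baseline, provided the groups compared are those randomised. Here the informants enter after allocation, by attending or by being recommended by a director who knows the centre's arm. The output is themes, not a scored outcome. So the comparison loses most of what randomisation would have given it. It can be shown, but it does not establish efficacy.

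**Step 3. Direction of the 3-month material.** The photo request presupposes that loose parts play supports physical literacy. Against that, Section 3.2.4 also lists challenges among the question topics and asks what made use difficult. That admits unfavourable comment, mostly on use of the materials and less on absence of effect. The material leans one way; it is not closed to the other.

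**Step 4. Who the 3-month informants are.** Section 3.2.4 gives 9 attendees from the original cohort and 15 from the new one.

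- Total: 9 + 15 = 24; new-cohort share 15/24 = 62.5%.
- Adding the 4 educators seen on site as extra informants: 24 + 4 = 28. Their cohort is not stated. If none is new cohort, 15/28 = 53.6%; if all are, 19/28 = 67.9%.

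So more than half come from the three intervention sites recruited in November 2017 (Section 2.2.1), for which no concurrently recruited control centre is described. This describes the composition of the evidence and does not measure bias.

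**Step 5. What does match the comparative objective.** Section 3.4 also plans linear mixed models with a random effect for centre, comparing children in the two groups by intention to treat. That is the only analysis described that answers the question against standard practice. The section does not say how it ranks against the sentence in which qualitative and RE-AIM data settle effectiveness.

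**Step 6. Internal consistency.** The Abstract and Section 3.4 speak of focus groups with intervention sites; Section 3.2.4 invites both arms at 6 months. These passages need to be reconciled.

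**The case against.** The case on the other side has several parts.

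- *The sentence names RE-AIM as a joint source.* True. Section 2.1 lists effectiveness as one RE-AIM dimension, and the figure setting it out is not shown, so that part may draw on the controlled child outcomes. This stands: focus groups are not the sole arbiter. It does not make the one-arm half of the pair suitable for the task.
- *The data are not closed to bad news.* A reader might infer that the plan can only return a favourable answer. The documents do not support that: challenges were asked about, and the ongoing photo documentation had an open prompt. The request for supportive photos applies to the 3-month session.
- *There is a between-arm contrast.* A reader might infer that there is none. That is also wrong: control centres were invited at 6 months and control-group parents were interviewed. The contrast is post-only and rests on selected informants.
- *Qualitative data before the intervention.* Section 2.2.1 says in general terms that qualitative data were collected at baseline. The detailed procedures describe no baseline focus group or interview, so the point rests on those procedures being complete.
- *The child outcomes have their own controlled test.* This stands. A reader might infer that the trial may declare success over null child results; nothing in the text says that qualitative findings override the mixed models.
- *The three added sites.* A reader might call them non-randomised. Section 2.2.1 says that all 19 centres were randomly allocated, so that is an inference, and this point does not need it.
- *Timing.* Data collection ended in September 2018, so rewriting the objectives now would be post hoc. This is fair, and it argues for qualifying the conclusions and leaving the objectives as they were stated.

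**Conclusion.** The point holds in a limited form. Section 3.4 is wrong as written where it lets intervention-site photo and focus group material help determine effectiveness, and where it expects focus groups and interviews to show that attitudes improved and understanding increased. The 3-month material has no control group and no described baseline, and includes photos requested as favourable. The educator and parent evidence offers at most a post-only contrast among selected informants.

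The size cannot be put as a bias or an error rate: no estimate, model or sample size changes. What changes is what may be concluded. Objectives 2 and 3 cannot yield an efficacy claim against standard practice, and the effectiveness conclusion should rest on the controlled child analysis. This assumes that Sections 3.2 and 3.3 list all educator and parent data collection. A baseline qualitative round would supply a before-after view, but would not cure the one-arm 3-month material.

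**What to change.** 1. In Section 3.4, limit the qualitative data to describing experience, implementation, acceptability and perceived mechanisms.
2. State there that effectiveness is judged on the between-group mixed-model analysis of child outcomes.
3. Leave objectives 2 and 3 as stated, but report conclusions on them as exploratory, perceived changes. Show the 6-month control-arm focus groups and the control-parent interviews alongside, labelled as post-only and drawn from attendees and recommended parents.
4. Reconcile the Abstract and Section 3.4, which name intervention sites only, with Section 3.2.4, which invites both arms at 6 months. Say also what baseline qualitative data Section 2.2.1 refers to.

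The cost is wording and presentation; no new data are needed. The downside is weaker claims for objectives 2 and 3.

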## 4. Discussion

As the purpose of this paper is to describe the purpose, study design and methodology of the PLEY loose parts intervention, no results are included in this paper. It is hypothesized that children in centres exposed to the loose parts intervention will experience greater increases in physical literacy, PA and active outdoor play than the usual practice centres. Previous studies similar to this have reported changes (mean(95%CI)) of −0.2(−1.7 to 1.3) in physical activity between groups [53], and 2.5 (−1.7 to 6.7) in the sum of scores for fundamental movement skills between groups [40]. It is also hypothesized that parents and educators involved in the intervention centres will gain a greater understanding of physical literacy, PA, and active outdoor play. It is hypothesized that educators will be exposed to an increase of risk-taking behaviors with the introduction of loose parts into outdoor play environments and that they will begin to recognize their children’s ability to assess risk independently. Finally, it is also hypothesized that the loose parts intervention has the potential to clarify the role of the educator as a guide, a mentor and a co-player in outdoor environments.

This study consists of various strengths and limitations to be acknowledged. The major strength of this study lies in the uniqueness of an outdoor play intervention with the use of loose parts, the inclusion of urban, suburban, and rural regions of Nova Scotia, and in the measurement of child, parent and educator components. The limitations of this study include the dropout rate of children, which resulted in a lower sample size during the post-testing, and that not all components of physical literacy were measured as part of this study, given the age of the child.

## Figures and Tables

**Figure 1 mps-02-00027-f001:**
[figure not shown]
RE-AIM framework outline for the Physical Literacy in the Early Years (PLEY) project.

**Figure 2 mps-02-00027-f002:**
[figure not shown]
PLEY project components

**Figure 3 mps-02-00027-f003:**
[figure not shown]
Flow diagram of participant numbers (children).
